### 7.3 Withdrawal/follow-up

12 participants were excluded during the 8-week weight loss period between enrollment and randomization due to insufficient weight loss, malignancy, surgery, and withdrawal of consent. 14 lost to follow-up in the liraglutide arm between randomization due to non-compliance, treatment emergent adverse effects (TEAEs) or other reasons. 13 lost to follow-up in the placebo arm between randomization due to non-compliance, TEAEs, or other reasons.

## 7.4 Patient characteristics

Patients will be described with according to demographics, comorbidities, laboratory values and point of care (POC) measurements, separately and combined for the two randomized groups. Data will be from enrollment visit (week -8).

## 8 ANALYSES

### 8.1 Outcome definitions

*Primary outcome:* Changes in serum NGAL following the 8-week intensive weight loss period (week -8 to week 0). Blood samples acquired from all participants at week -8 and 0 will be analyzed to determine serum NGAL (mg/ml). Plasma samples have been assessed using a commercially available electrochemiluminescence assay: NGAL/LCN2 R-plex Assay® produced by Meso Scale Discovery Inc (MSD), Rockville, Maryland, USA.

*Secondary outcomes:* Changes in serum NGAL in both liraglutide and placebo arm at week 0 and 52.

*Exploratory outcomes:* Changes in [i] CRP, [ii] total-Cholesterol, [iii] HDL, [iv] LDL, [v] TG, [vi] glucose, [vii] HbA1c, [viii] creatinine, [ix] eGFR, [x] ALAT, [xi] systolic BP, [xii] diastolic BP, [xiii] body weight and [xiv] BMI, in the two periods: enrollment to baseline (week -8 to week 0) and baseline to study end (week 0 to week 52).

## 8.2 Analysis methods

The effect of the initial 8-week dietary intervention on the primary outcome variable serum NGAL will be analyzed using paired t-test. In the mITT population crude mean change will be estimated together with the associated 95% confidence interval and  $p$ -value corresponding to the test of the hypothesis of no difference between time points (i.e., the null hypothesis).

The effect of liraglutide and placebo (week 0 to 52) on the secondary endpoint change in serum NGAL will be determined using an ANCOVA model adjusted for stratification factors recorded at enrollment ([i]Sex, [ii] Age category and [iii] Obesity Class), and the level of the outcome at baseline (week 0). From this model, the observed differences in least squares means for change between liraglutide treatment and placebo will be estimated together with the associated 95% confidence interval and the  $p$ -value corresponding to the test of the hypothesis of no difference between treatments (i.e., the null hypothesis).

In the case of missing data at week 52, missing data will be handled using multiple imputations assuming data missing at random (MAR). A simple non-responder imputation (Enrollment Observation Carried Forward [EOCF]) will be done as a sensitivity analysis, assuming data missing not at random (MNAR).

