### 4.3 Study Objectives

- *Primary objective:* To evaluate changes in serum NGAL in overweight individuals with KOA undergoing a significant ( $\geq 5\%$ ) weight loss from an IDI from week -8 (enrollment) to week 0 (randomization).
- *Secondary objective:* To compare the effect of liraglutide, relative to placebo on changes in serum NGAL from week 0 (randomization) to week 52 (end of trial), in individuals with KOA who have achieved a significant ( $\geq 5\%$ ) weight loss through the initial 8-week dietary intervention.
- *Exploratory objectives:*
  - To evaluate changes in [i] C-reactive protein (CRP), [ii] total-Cholesterol, [iii] high-density lipoprotein cholesterol (HDL), [iv] low-density lipoprotein cholesterol (LDL), [v] triglycerides (TG), [vi] glucose, [vii] glycated hemoglobin (HbA1c), [viii] creatinine, [ix] estimated glomerular filtration rate (eGFR), [x] alanine aminotransferase (ALAT), [xi] systolic blood pressure (BP), [xii] diastolic BP, [xiii] body weight and [xiv] BMI in overweight individuals with KOA who undergo a significant ( $\geq 5\%$ ) weight loss from an 8-week intensive dietary intervention.
  - To compare the effect of liraglutide, relative to placebo, on changes in [i] CRP, [ii] total-Cholesterol, [iii] HDL, [iv] LDL, [v] TG, [vi] glucose, [vii] HbA1c, [viii] creatinine, [ix] eGFR, [x] ALAT, [xi] systolic BP, [xii] diastolic BP, [xiii] body weight and [xiv] BMI, from baseline (week 0) to week 52, in overweight individuals with KOA who have achieved a significant ( $\geq 5\%$ ) weight loss through the initial 8-week dietary intervention.

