## **5.8 Timing of outcome assessments**

The outcomes investigated in this trial are assessed at weeks -8, 0, and 52.

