# **6 STATISTICAL PRINCIPLES**

## **6.1 Confidence intervals and P values**

*Level of statistical significance and use of confidence intervals:* All applicable statistical tests will be two-sided and will be performed using a 5% significance level. All confidence intervals presented will be 95% and two-sided.

*Rationale for any adjustment for multiplicity:*

Due to the explorative design of this study, we will not adjust for multiplicity in this study. P values will be reported for all analyses, while the interpretation will be based on the hierarchy of which these will be analyzed as indicated by the order of outcomes in the objectives.

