## **6.2 Analyses populations**

We will analyze all patients randomized at week 0 regardless of their eligibility or adherence during the original trial but with NGAL data available at enrollment (week -8). This is a modified intention-to-treat (mITT) population of the original ITT population in the LOSE-IT trial.

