### **7.2 Eligibility**

Inclusion criteria in the original trial as described in suppl. material *Am J Clin Nutr* 2021;**113**:314–23. doi:10.1093/ajcn/nqaa328 [2]:

- Informed consent obtained
- Clinical diagnosis of knee OA (American College of Rheumatology [ACR] criteria) with early to moderate radiographic changes (Kellgren-Lawrence [KL] grades 1, 2, or 3)
- Age  $\geq 18$  years and  $< 75$  years
- Body mass index (BMI)  $\geq 27$  kg/m^2
- Stable body weight during the previous 3 months ( $< 5$  kg self-reported weight change)
- Motivated for weight loss
- Achieved at least 5% weight loss during the initial 8-week IDI (assessed at allocation visit; T0)

In addition to this we required

- NGAL data at enrollment (week -8)
- Randomization (week 0)

Exclusion criteria in the original trial:

- On-going participation, or participation within the last 3 months, in an organized weight loss program (or within the last 3 months)
- Current or history of treatment with medications that may cause significant weight gain for at least 3 months before this trial
- Current use or use within 3 months before this trial of GLP-1 receptor agonist, pramlintide, sibutramine, orlistat, zonisamide, topiramate, or phentermine
- Type 1 diabetes
- Type 2 diabetes treated with glucose-lowering drugs other than metformin
- Arthroplasty in target knee joint (most symptomatic knee at screening)
- End stage disease in target knee joint (Kellgren-Lawrence grade 4)
- Immuno-inflammatory disease
- Chronic wide-spread pain
- Pregnancy or insufficient anti-conception therapy for female fertile patients
- Breast-feeding
- Estimated glomerular filtration rate (eGFR) < 60 ml/min/1.73 m^2
- Alanine aminotransferase (ALT) or aspartate aminotransferase (AST) > 3 x above upper normal range (UNR)
- Elective surgery scheduled during the trial duration period, except for minor surgical procedures
- Surgical procedures such as arthroscopy or injections into a knee within 3 months prior to enrollment
- Previous surgical treatment for obesity (excluding liposuction >1 year before trial entry)
- Thyroid stimulating hormone (TSH) outside of the range of 0.4-6.0 mIU/L
- Obesity secondary to endocrinologic or eating disorders, or to treatment with medicinal products that may cause weight gain
- Family or personal history of medullary thyroid carcinoma or multiple endocrine neoplasia type 2
- Inflammatory bowel disease

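### The NGAL ANCOVA in section 8.2 does not use the week -8 NGAL value that every analysed patient has; prespecifying it may sharpen the only randomised NGAL comparison at little cost

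*SAP*

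**What the plan says.** The secondary objective in section 4.3 reads: "To compare the effect of liraglutide, relative to placebo on changes in serum NGAL from week 0 (randomization) to week 52 (end of trial"). For that comparison section 8.2 states that the effect "will be determined using an ANCOVA model adjusted for stratification factors recorded at enrollment", namely sex, age category and obesity class, and adds "the level of the outcome at baseline (week 0"). The week -8 level of the outcome is not among the covariates.

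Section 5.8 says: "The outcomes investigated in this trial are assessed at weeks -8, 0, and 52". Section 6.2 confines the analysis to randomised patients "with NGAL data available at enrollment (week -8"), and section 7.2 repeats "NGAL data at enrollment (week -8") as an added requirement. A week -8 NGAL value is therefore present for the whole mITT population by definition. Neither section sets the same condition for week 0 NGAL, which the model does use.

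For missing week 52 values, section 8.2 plans multiple imputation under MAR and does not name the variables in the imputation model. On testing, section 6.1 says: "All applicable statistical tests will be two-sided and will be performed using a 5% significance level". The power statement in section 5.4 covers body weight and KOOS-Pain in the original trial. The SAP gives no effect size, standard deviation, visit-to-visit correlation or power target for NGAL.

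**The concern.** The primary NGAL outcome is a single-group change over the diet period. The week 0 to 52 ANCOVA is therefore the only randomised evidence on NGAL, and its sample size is fixed by a completed trial. Covariates are one of the few remaining ways to gain precision.

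A single biomarker reading mixes a person's usual level with assay and day-to-day noise. A second reading before randomisation can recover part of that usual level. Because it precedes allocation, adjusting for it introduces no bias.

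There is also a design reason to think that week -8 may add something. Week 0 is read at the end of an intensive diet, whereas week -8 follows a required period of stable weight. If patients drift back towards their usual level during the year, week -8 tells something about week 52 that week 0 does not. The plan's own sensitivity analysis (EOCF) puts the week -8 value in place of a missing week 52 value, yet the main model does not use week -8 as a predictor.

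**Working it through.** The SAP has no NGAL precision or power figure to reproduce. Its figure of 150 participants belongs to two other outcomes and comes without standard deviations.

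**Inputs**
- From the SAP: the covariate list (8.2), completeness of week -8 NGAL (6.2, 7.2), 1:1 allocation (5.1), 150 participants in the original design (5.4), and 14 and 13 lost to follow-up (7.3).
- Assumed: the three correlations, taken within arm and after the strata, with equal variance at each visit. They are r0 (week 0 with week 52), rm (week -8 with week 52) and r (week -8 with week 0).
- Assumed: N = 150, because the SAP does not state the mITT size.

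**Formulas**
1. Once week 0 is a covariate, modelling the change or the week 52 value gives the same treatment effect and residual variance. With week 0 only, that variance (as a share of the week 52 variance) is v1 = 1 - r0².
2. Adding week -8 multiplies it by 1 - p², where p = (rm - r0·r) / √[(1 - r0²)(1 - r²)] is the partial correlation of week -8 with week 52 given week 0.
3. Going from four covariates to five multiplies the variance of the treatment effect by about (N - 7)/(N - 8) = 143/142 = 1.0070, or 1.0035 on the standard error (SE).

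**Worked cases**
- Equal 0.5: v1 = 0.750. p = (0.5 - 0.25)/0.75 = 0.333, so p² = 11.1%. The SE ratio is √(0.8889 × 1.0070) = 0.946.
- Pattern (r0, rm, r) = (0.6, 0.6, 0.8): p = (0.6 - 0.48)/√(0.64 × 0.36) = 0.12/0.48 = 0.25, so p² = 6.25%. The SE ratio is √(0.9375 × 1.0070) = 0.972.
- Markov: rm = r0·r, so p = 0 and only the cost of the extra term remains.

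| Assumed (r0, rm, r) | Fall in residual variance | Change in SE, N = 150 |
|---|---|---|
| Markov, e.g. (0.5, 0.25, 0.5) | 0% | +0.35% |
| Mild decay (0.7, 0.6, 0.8) | 0.9% | -0.1% |
| Mild decay (0.6, 0.5, 0.7) | 2.0% | -0.6% |
| (0.6, 0.6, 0.8) | about 6% | -2.8% |
| Equal 0.5 | 11.1% | -5.4% |
| Equal 0.7 | 17.0% | -8.6% |

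Other decay patterns gave variance reductions from 0.2% at (0.6, 0.5, 0.8) to 5.2% at (0.6, 0.55, 0.7). An equal correlation of 0.9 would give 22.4%, but the conclusion does not lean on a value that high.

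**Checks**
- Both models were simulated with complete data (N = 150, 6,000 runs, no treatment effect). The ratios of mean SE were 0.9455 (equal 0.5), 0.9145 (equal 0.7), 0.9936 for (0.6, 0.5, 0.7), and 1.0034 to 1.0035 (Markov). The mean estimate lay within 0.004 of zero in both models throughout, so neither is biased.
- With 150 - 14 - 13 = 123 patients the variance ratios do not change. The SE ratios become 0.947 (equal 0.5), 0.915 (equal 0.7) and 1.0043 (Markov).

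**The case against.** The strongest reply is that nothing here is wrong. ANCOVA on the stratification factors and the baseline outcome is a standard, unbiased choice, and one more prognostic covariate could be proposed for almost any trial. That stands: this is an improvement that the plan does not take, not an error or a contradiction.

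A reader might go further and infer that the model certainly wastes precision. The documents do not support that. The gain depends wholly on correlations that the SAP does not give. The visits lie 8, 52 and 60 weeks apart, so the two early readings may resemble each other more than either resembles week 52. Even mild decay brings the gain down to 1-2%, and under a Markov pattern there is none.

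A reader might also want the gain expressed as power. That needs an NGAL effect size and standard deviation, which section 5.4 lacks, and a calculation under the planned multiple imputation rather than among completers. Nor can one infer that week -8 NGAL is left out of the imputation model: section 8.2 does not list its variables either way.

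Finally, sections 6.2 and 7.2 guarantee week -8 data for NGAL only. The case does not carry over unchecked to the exploratory outcomes. For body weight and BMI, obesity class at enrolment already brings some week -8 information into the model.

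What survives is the imbalance between cost and benefit. The worst case among the patterns examined is an SE about 0.35% larger, and several plausible patterns make it roughly 3-9% smaller.

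**Conclusion.** The point holds as a suggestion for a better prespecified model. The ANCOVA in section 8.2 is valid and unbiased, but it leaves unused a pre-randomisation NGAL value that every mITT member has. Using it may improve the precision of the only randomised NGAL contrast.

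Over the patterns in the table, the residual variance falls by 0% to 17% and the SE changes by about +0.35% to -9%. These figures rest on assumed correlations, equal variances across visits and N = 150. They are illustrations, not estimates for this trial, and support no claim of a specific power gain.

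**What to change.** In section 8.2, before the NGAL analysis is run, list the ANCOVA covariates as sex, age category, obesity class, week 0 NGAL and week -8 NGAL. State there that the imputation model for week 52 NGAL includes week -8 NGAL, so that the imputation and analysis models agree.

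Extend the same covariate to the exploratory outcomes in Table 3 only where their week -8 values are confirmed to be essentially complete.

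For NGAL the cost is one term in the text and code and one degree of freedom, with no new data. Timing matters: added before the analysis, the covariate is prespecified, as section 3 intends for the plan as a whole; added afterwards, it could look selected.

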## 8.3 Harms and adverse events

Not applicable

## 8.4 Statistical software

The analysis will be carried out using R version 4.1.3 (or newer).

## 12 TABLE AND FIGURES

Figure 1: Flow diagram of the population

Table 1: Characteristics of the participants at enrollment

Table 2: Changes from week -8 to week 0

Figure 2. Serum NGAL (panel A) BMI (panel B) at different time points

Table 3: Changes from week 0 to week 52

Appendix 1: Changes from week -8 to week 0 (the mITT Population), with missing data replaced using non-responder imputation (EOCF)

Appendix 2: Changes from week 0 to week 52, with missing data replaced using non-responder imputation (EOCF)

Figure 1. Flow diagram of the population

[figure not shown]

**Table 1. Characteristics of the participants at enrollment 8 weeks prior to randomization (the mITT Population)**

|                                | All (n=) | Liraglutide 3 mg*
(n= ) | Placebo*
(n= ) |
|--------------------------------|----------|----------------------------|-------------------|
| Female sex, n (%)              |          |                            |                   |
| Age, years                     |          |                            |                   |
| Diabetes, n(%)                 |          |                            |                   |
| CVD, n(%)                      |          |                            |                   |
| CKD, n(%)                      |          |                            |                   |
| Height, cm                     |          |                            |                   |
| Body weight, kg                |          |                            |                   |
| BMI, m/kg          |          |                            |                   |
| Systolic Blood Pressure, mmHg  |          |                            |                   |
| Diastolic Blood Pressure, mmHg |          |                            |                   |
| Laboratory variables:   |          |                            |                   |
| NGAL, ng/mL                    |          |                            |                   |
| CRP, mg/dL                     |          |                            |                   |
| Cholesterol, mg/dL             |          |                            |                   |
| HDL, mg/dL                     |          |                            |                   |
| LDL, mg/dL                     |          |                            |                   |
| TG, mg/dL                      |          |                            |                   |
| Glucose mg/dL                  |          |                            |                   |
| HbA1c mmol/ml                  |          |                            |                   |
| Creatinine, mg/dL              |          |                            |                   |
| eGFR, mL/min                   |          |                            |                   |
| ALAT, U/L                      |          |                            |                   |

Values are mean (SD) unless otherwise indicated. CVD: Cardiovascular disease, CKI: Chronic Kidney Insufficiency

\*Patients were not allocated into groups until week 0, hence, the groups did not formally exist from enrollment and until the end of the run-in diet period (week –8 to 0)

**Table 2. Changes from week -8 to week 0 (the mITT Population)**

| Variables                     | N | Change | 95%CI | p-value |
|--------------------------------------|-----------------|---------------|--------------|-----------------------|
| NGAL, ng/mL                          |                 |               |              |                       |
| CRP, mg/dL                           |                 |               |              |                       |
| Cholesterol, mg/dL                   |                 |               |              |                       |
| HDL, mg/dL                           |                 |               |              |                       |
| LDL, mg/dL                           |                 |               |              |                       |
| TG, mg/dL                            |                 |               |              |                       |
| Glucose mg/dL                        |                 |               |              |                       |
| HbA1c mmol/ml                        |                 |               |              |                       |
| Creatinine, mg/dL                    |                 |               |              |                       |
| eGFR, mL/min                         |                 |               |              |                       |
| ALAT, U/L                            |                 |               |              |                       |
| Systolic Arterial Pressure,
mmHg  |                 |               |              |                       |
| Diastolic Arterial Pressure,
mmHg |                 |               |              |                       |
| Body weight, kg                      |                 |               |              |                       |
| BMI, m/kg                |                 |               |              |                       |

Values will be reported as means with 95% CIs unless otherwise indicated. Missing data will be handled using multiple imputation (assuming ‘MAR’).

[figure not shown]

**Figure 2. Serum NGAL (panel A) BMI (panel B) at different time points**

*(Values will be estimated based on the same models as used for table 2 and 3)*

**Table 3. Changes from week 0 to week 52**

| Variables                         | Liraglutide 3 mg
(n= ) | Placebo
(n= ) | Difference
between groups
(95%CI) | p -value |
|-----------------------------------|---------------------------|------------------|-----------------------------------------|-----------------|
| NGAL, ng/mL                       |                           |                  |                                         |                 |
| CRP, mg/dL                        |                           |                  |                                         |                 |
| Cholesterol, mg/dL                |                           |                  |                                         |                 |
| HDL, mg/dL                        |                           |                  |                                         |                 |
| LDL, mg/dL                        |                           |                  |                                         |                 |
| TG, mg/dL                         |                           |                  |                                         |                 |
| Glucose mg/dL                     |                           |                  |                                         |                 |
| HbA1c mmol/ml                     |                           |                  |                                         |                 |
| Creatinine, mg/dL                 |                           |                  |                                         |                 |
| eGFR, mL/min                      |                           |                  |                                         |                 |
| ALAT, U/L                         |                           |                  |                                         |                 |
| Systolic Blood Pressure,
mmHg  |                           |                  |                                         |                 |
| Diastolic Blood Pressure,
mmHg |                           |                  |                                         |                 |
| Body weight, kg                   |                           |                  |                                         |                 |
| BMI, kg/m             |                           |                  |                                         |                 |

Values for the groups are presented as least squares means with corresponding standard errors, and differences between groups are presented as the differences between least squares means with 95% CIs unless otherwise indicated. Missing data will be handled using multiple imputation (assuming ‘MAR’).

**Appendix table 1. Changes from week -8 to week 0 (the mITT Population), with missing data replaced using non-responder imputation (EOCF)**

| Variables                  | N | Change | 95%CI | p-value |
|-----------------------------------|-----------------|---------------|--------------|-----------------------|
| NGAL, ng/mL                       |                 |               |              |                       |
| CRP, mg/dL                        |                 |               |              |                       |
| Cholesterol, mg/dL                |                 |               |              |                       |
| HDL, mg/dL                        |                 |               |              |                       |
| LDL, mg/dL                        |                 |               |              |                       |
| TG, mg/dL                         |                 |               |              |                       |
| Glucose mg/dL                     |                 |               |              |                       |
| HbA1c mmol/ml                     |                 |               |              |                       |
| Creatinine, mg/dL                 |                 |               |              |                       |
| eGFR, mL/min                      |                 |               |              |                       |
| ALAT, U/L                         |                 |               |              |                       |
| Systolic Arterial Pressure, mmHg  |                 |               |              |                       |
| Diastolic Arterial Pressure, mmHg |                 |               |              |                       |
| Body weight, kg                   |                 |               |              |                       |
| BMI, m/kg             |                 |               |              |                       |

Values will be reported as means with 95% CIs unless otherwise indicated.

